#### Sample request and reporting

Blood samples are requested by the personnel at the cardiac department according to the patient’s randomization status (for randomization process; *see below*). Requests for blood sample analysis are done by ordering pre-defined bundles/packages of analyses. This ensures that all patients have both copeptin and hs-cTnT measured in both pre-hospital and first in-hospital blood samples, but only results relevant to the randomization group are passed on to the clinicians, as follows:No copeptin results and no result of the 1-h troponin in the standard groupResults of pre-hospital but not in-hospital copeptin in the accelerated diagnostic group

All hs-cTn analyses are ordered with prioritization, meaning that the results have to be reported within 1 h.

Results are reported electronically from the hospital laboratory system (LABKA II; CSC Healthcare EMEA/DXC Technology, Boeblingen, Germany) to the clinicians via the electronic patient management system (Midt-EPJ; Systematic, Aarhus C, Denmark). All blood sample analysis results (including the blinded pre-hospital copeptin in the standard group and the in-hospital copeptin) can be retrieved from LABKA on request.

#### General in-hospital patient management

The patients are received by a doctor and a nurse at the department of cardiology, and the patient is immediately put on continuous ECG surveillance. The initial assessment includes ECG, vital signs, thorough questioning of medical history and present symptoms, and a physical examination. A laboratory technician is called for prompt blood sampling. All blood sample analyses are performed at a central hospital laboratory. Acute echocardiography and additional diagnostic procedures such as imaging, stress testing and additional biochemistry are available at all centres. Supplementary standard diagnostic workup for each centre is described below:Aarhus: Echocardiography is performed as standard in connection with first evaluation by the attending physician. Chest x-ray is performed on demand according to the clinical presentation. First and second evaluations (including follow-up of initial blood sample analyses) are often performed by the same physician.Viborg: Echocardiography is performed as standard in connection with the secondary evaluation. Chest x-ray is performed on demand according to the clinical presentation. Patients in Viborg are generally followed during evening rounds by a senior physician or on the general rounds the next day.Horsens: Echocardiography is performed according to the clinical presentation. Chest x-ray is performed as standard on all patients. First and secondary evaluations (including follow-up of initial blood sample analyses) are often performed by the same physician.

### Outcomes

#### Outcome measures

##### Primary outcome measures

LOS:Time (hours and minutes) from admission to discharge from cardiac department (either to home or to a non-cardiac department)Retrieved from the patient administrative system, the patient’s medical record and the national health registryWill be evaluated when 300 patients have been discharged after rule-out of AMI at each site (patients discharged from hospital within 12 h of admission)Combined MACE proportionCombined endpoint of MACE (only first event per patient), consisting of the following (Occurring within time from randomization to 30 days after randomization):All-cause mortalitySurvived cardiac arrestConfirmed acute coronary syndrome (ACS) or re-admission with ACSNon-scheduled coronary interventionLife-threatening arrhythmiasWill be evaluated when inclusion of all patients is completed

(*See below* for detailed description of each component of the combined endpoint.)

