## Abstract

**Background:**

Suspicion of acute myocardial infarction (AMI) is among the most common reasons for admission to hospital in Denmark. Owing to this suspicion, an estimated 50,000 patients are admitted every year. Only 15–20% are finally diagnosed with AMI, whereas 40% are discharged after rule-out of AMI and without initiation of any treatment or need for further admission. In patients discharged after rule-out, the current diagnostic protocol, using consecutive troponin measurements, results in an average length of stay (LOS) of 8–12 h. This leads to overcrowding in both the emergency departments and coronary care units. Measuring copeptin and high-sensitivity cardiac troponin (hs-cTn) upon hospital arrival has shown potential for early rule-out of AMI. However, the diagnostic performance may be improved by accelerating the copeptin measurement of blood sampled already in the pre-hospital phase. Additional evidence on LOS reduction and safety of the rule-out strategy in a large cohort of all-comers is needed.

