#### Additional in-hospital blood samples

Patients randomized to the standard diagnostic group will have a second (third if you count in the extra study sample; *see below*) blood sample taken after 3–6 h (*see below*). Patients randomized to accelerated diagnostics will only have a second blood sample drawn if copeptin, troponin or both are elevated in the initial blood samples or if requested by the attending physician. Second and later hs-cTn samples and analysis are performed as described above, except that copeptin is not analysed, and the remaining plasma is not stored. As a supplement, all patients in the standard diagnostic group will have an extra blood sample drawn 1 h after the first in-hospital blood sample. This sample is only analysed for hs-cTn, and no blood is stored. The extra sample is not drawn in the accelerated diagnostic group, because some of these patients potentially could be discharged at or before this time point.

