##### Confirmed diagnosis of ACS during index admission or re-admission with ACS

Number of ACS events (only first event per patient) divided by number of patientsThe national health registry is used to determine whether the patient is confirmed of having or being re-admitted with ACS, from time of admission to discharge and within 30, 90 and 365 days after randomization. The endpoint committee adjudicates ACS, blinded to the initial randomization. The 2015 ESC Guidelines for the management of ACS in patients presenting without persistent ST-segment elevation and the Universal Definition of Myocardial Infarction will be used to evaluate if the patient had ACS and subsequently classify it as follows:○ Unstable angina pectoris (UAP)○ Non-ST-elevation myocardial infarction (NSTEMI)STEMI○ Bundle branch block myocardial infarctionWill be evaluated when inclusion of all patients is completed

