#### Sample size calculation

Thirty-day MACE including all-course mortality is expected to be between 5.5% and 7.5% [7, 20]. Using a MACE rate of 6.5%, a non-inferiority limit of 2%, alpha = 2.5% and power (beta) = 80% will result in the need for enrolment of 4772 patients to confirm a difference in 30-day MACE rate of more than 2%.

Regarding LOS, in 2012, the average LOS of patients admitted with suspected AMI at Aarhus University Hospital was 12 h (SD = 6.1). It is expected that 40% of patients in the accelerated group can be discharged within 3 h after admission [7, 20], thus resulting in an estimated 1–1.5 h reduction of LOS in patients discharged without AMI.

Inclusion of about 4800 patients in total will enable us to show a difference in LOS of 54 min with a power > 90%. To show an average 1.5-h reduction in LOS (under the condition that 40% in the accelerated group are discharged within 3 h), 337 patients in each randomization group discharged after early rule-out of AMI (patients discharged from hospital within 12 h of admission) are needed (μ = 12, SD = 6.1, alpha = 5%, beta = 90%). To take differences between sites into account, we increased the number of discharged patients by one-third to 450 patients per randomization group. Distributing the patients equally between sites (150/site/randomization group), 300 patients discharged after rule-out of AMI (patients discharged from hospital within 12 h of admission) in each site are needed.

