#### Manual adjudication

The manual adjudication is performed by an independent endpoint committee consisting of six to nine (depending on the final number of suspected events; *see below*) Danish independent cardiologists from outside the Central Denmark Region (*see* Additional file 4). Because of the high level of completeness and quality of the Danish health care registries and available electronic databases, a complete review of medical records from all patients is not considered to be necessary. Instead, only selected suspected events are presented to and evaluated by the endpoint committee (*see below*). Each suspected event is independently evaluated by two cardiologists. The adjudication is based on patient medical records, laboratory results and other supplementary information on request from the adjudicators. The endpoint committee is, per protocol, blinded to randomization status; the assigned group may be derived de facto from the medical record in most cases. All other information is available in the adjudication process.

All-cause death is accepted if the patient is registered as dead in the social security register. Survived cardiac arrest is accepted if a resuscitation attempt by a health care professionals is registered in the patient medical record and the patient survived to discharge. Non-scheduled re-vascularizing coronary intervention (PCI or CABG) is accepted if a non-scheduled coronary re-vascularization is registered in the patient medical record. Life-threatening, treatment-demanding arrhythmias are accepted if third-degree atrioventricular block, ventricular tachycardia or ventricular fibrillation resulting in initiation of treatment is registered in the patient medical record. Re-admissions with ACS (including NSTEMI types 1–5, STEMI types 1–5 and UAP) are accepted according to the criteria described in the Universal Definition of AMI (*see* Additional file 4 for full description). Myocardial injury is adjudicated by the endpoint committee but is not included as part of the endpoint of re-admissions with ACS.

The adjudication is documented in TrialPartner by each adjudicator, and the event is confirmed if both adjudicators agree. In case of disagreement between the two reported adjudications, the event is evaluated by a third member of the endpoint committee (*see* Additional file 4).

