## Discussion

Early rule-in/rule-out of AMI has been a hot subject for the past 5–10 years. Although patients suspected of AMI are abundant, only about one-tenth of them actually have had an AMI. Biomarker testing is a keystone in AMI diagnostics. Because no diagnostic strategy can rely entirely on biomarker testing, however, biomarker testing should always be performed in parallel with a thorough clinical evaluation.

Several new strategies to improve and accelerate AMI diagnostics have been suggested. These include troponin-only strategies optimizing the ESC standard algorithm for the diagnosis of NSTEMI (0 h/1 h, 0 h/2 h and 0 h algorithms), strategies combining troponin measurement with clinical data (Manchester Acute Coronary Syndromes decision rule, heart score) and dual-marker strategies combining troponin with other biomarkers (e.g., copeptin and Heart-type fatty acid-binding protein).

In the troponin-only strategies, the measurements of hs-cTn are advanced timely, either by reducing time between samples (the delta-time) or by reducing the number of blood samplings. All of these are challenged by the delayed release of troponin after a myocardial infarction. Several retrospective studies have shown the troponin-only strategies to be effective and safe, but they have not been evaluated in larger, randomized trials.

A common weakness in all fast-diagnostics strategies is the inherent need to adjust the local clinical setup to fit the fast-track diagnostic approach to fully exploit the potential of these strategies. All relevant in-hospital diagnostics should be easily available and completed with no delay. Health care personnel should be available for clinical evaluation and decision-making at the time when biomarker results and results of other examinations are delivered.

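### The ACS part of primary MACE is defined in two conflicting ways; counting the presenting ACS tilts the non-inferiority test toward success and fits poorly with the 6.5% planning rate

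*Protocol article*

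**What the plan says.** - **Primary outcome measures.** MACE is a composite, first event per patient, "Occurring within time from randomization to 30 days after randomization". Its ACS component is confirmed "acute coronary syndrome (ACS) or re-admission with" ACS. The section refers the reader to the component descriptions that follow.
- **Component description.** Its heading reads "Confirmed diagnosis of ACS during index admission or re-admission with ACS". Index-admission ACS is therefore counted explicitly. Randomisation takes place on arrival at hospital (Intervention groups), so an index ACS will normally be confirmed inside the window.
- **Manual adjudication.** "Re-admissions with ACS (including NSTEMI types 1–5, STEMI types 1–5 and UAP) are accepted according to" the Universal Definition. No criterion is given here for ACS at the index stay, and the same paragraph calls the component an endpoint of re-admissions.
- **Sample size calculation.** "Thirty-day MACE including all-course mortality is expected to be between 5.5% and 7.5" per cent. The calculation uses 6.5%, a 2-point margin, alpha 2.5% and 80% power, and arrives at 4772 patients; 4800 are planned.
- **AMI share among suspected cases.** The abstract says "Only 15–20% are finally diagnosed with AMI"; the Discussion says "only about one-tenth of them actually have had an AMI".
- **Additional in-hospital blood samples.** Patients in the accelerated group "will only have a second blood sample drawn if copeptin, troponin or both are elevated". The same sentence adds that the attending physician may also request one.

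**The concern.** The Harms section names the danger of the accelerated strategy: a patient with AMI is sent home undetected. A safety endpoint should rise when that happens. If the presenting ACS itself scores as an event, a correct diagnosis counts against an arm and an undetected one may not. The standard arm is scheduled for a second troponin and the dual-negative part of the accelerated arm is not, so the opportunity to miss differs by arm. In a non-inferiority test the resulting bias runs toward success.

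The planning rate is the second issue. If index AMI counts, MACE in the enrolled patients cannot be lower than their AMI share. Both AMI figures in the article exceed the 5.5–7.5% it expects for MACE. A higher background rate widens the confidence interval around the difference, and the power is then lower than stated.

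**Working it through.** **1. The plan's own figure.** Inputs from Sample size calculation: p = 0.065 in both arms, margin 0.02, one-sided alpha 0.025, power 0.80, 1:1 allocation.

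n per arm = (1.960 + 0.8416)² × 2p(1−p) / 0.02² = 7.849 × 0.12155 / 0.0004 = 2385.1, rounded up to 2386. The total is 4772, as stated. The arithmetic is sound for a 6.5% rate.

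**2. Power at 4800 for other rates**, with no true difference:

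Power = Φ(0.02 / √(2p(1−p)/2400) − 1.96)

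| MACE rate | SE | Power at 4800 | N for 80% |
|---|---|---|---|
| 6.5% | 0.00712 | 80% | 4772 |
| 7.5% | 0.00760 | 75% | 5446 |
| 10% | 0.00866 | 64% | 7064 |
| 15% | 0.01031 | 49% | 10008 |
| 20% | 0.01155 | 41% | 12560 |

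The highest rate that keeps 80% power is 6.54%, so there is almost no slack.

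**3. Which rate applies if index ACS counts?** The 10% and 15–20% shares describe all patients with suspected AMI. The trial excludes suspected STEMI triaged directly to the tertiary centre, and the article does not say how much of AMI that removes. Taking the removed fraction s as an assumption, rate = share × (1 − s):

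| s (assumed) | Share 10% | Share 15% | Share 20% |
|---|---|---|---|
| 20% | 8.0%, power 72% | 12.0%, power 57% | 16.0%, power 47% |
| 35% | 6.5%, power 80% | 9.8%, power 65% | 13.0%, power 54% |
| 50% | 5.0%, power 89% | 7.5%, power 75% | 10.0%, power 64% |

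These rates are for AMI only. Unstable angina, and death, arrhythmia or unscheduled intervention without AMI, would add to them.

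**4. Direction of the bias.** For a patient who has ACS at presentation, under the definition that includes index ACS:

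| Course | Events counted |
|---|---|
| ACS found at the index stay | 1 |
| ACS missed, then re-admission, death or another component by day 30 | 1 |
| ACS missed, nothing recorded by day 30 | 0 |

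A miss never adds an event and can remove one. If A is the index ACS rate, m the extra fraction missed in the accelerated arm and r the fraction of the missed with an event by day 30, the difference shifts by −A·m·(1−r).

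The documents give neither m nor r. As an illustration only, take A = 15% and r = 25–50%:

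- m = 1%: 0.15 × 0.01 × (0.50 to 0.75) = 0.075 to 0.11 points
- m = 5%: 0.375 to 0.56 points
- m = 10%: 0.75 to 1.1 points

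The sign is fixed by the definition. The size ranges from negligible to more than half the margin, depending entirely on assumed values.

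**5. Under the re-admission definition**, the missed patient who returns scores 1 and the correctly diagnosed patient scores 0 for the presenting ACS. A miss can then add an event, and 6.5% no longer conflicts with the AMI share.

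**The case against.** The strongest reply is that the re-admission definition may be the operative one. The adjudication section uses it twice and refers to a supplementary file for the full criteria, which is not shown. The Discussion describes the MACE components as consequences of an AMI, which suits that reading. Under it, most of the problem disappears. This stands as a reason not to treat index ACS as settled. It does not remove the conflict, because the two places that define the endpoint both include index ACS.

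A reader might go further and infer that 80% power is unattainable, or that it should be restated as 41–64%. The document does not support either. The AMI shares are for all suspected cases, suspected STEMI is excluded, and the sources of the 6.5% are not shown, so it is unknown whether that rate already includes index events. Selection may also run the other way, because patients with miscellaneous symptoms and no risk factors go to the emergency department and the trial enrols CCU admissions.

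A reader might also infer that dual-negative patients never have a second troponin, or that a missed AMI counts only if the patient returns. Neither is right. The physician may request a repeat at any time, and death, cardiac arrest and the other components count too. Nor can any particular size of bias be read from the document.

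Finally, some protection exists. ACS is also a separate outcome from admission to discharge, each component has its own regression model, and re-admissions within 24 hours of discharge are reviewed with the DMC. These help interpretation, but the non-inferiority conclusion rests on the composite.

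**Conclusion.** The point holds in this form. The ACS component of the primary safety endpoint has two incompatible definitions. Under the one that counts index ACS, missed diagnoses can only leave the event count unchanged or reduce it, which biases the comparison toward non-inferiority. The direction follows from the scoring rule and needs no assumption about the AMI share; the size cannot be estimated from the document.

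The 6.5% rate is hard to reconcile with that definition. It survives only if the lowest AMI share applies, the STEMI exclusion removes at least about a third of AMI (10% × 0.65 = 6.5%), and the other components add almost nothing. Otherwise power is below 80%: 64% if the rate is 10%, 49% if it is 15%. These are conditional figures, computed at zero true difference, and not a forecast for the enrolled population. The stated sample size is correct for the rate it assumes.

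**What to change.** Before any by-arm MACE analysis:

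1. Align Primary outcome measures and the ACS component description with Manual adjudication, so that the primary ACS component is re-admission with ACS within 30 days of randomisation. Make clear that a return with an ACS missed at the index stay counts.
2. Treat non-scheduled coronary intervention for the index ACS in the same way: not a primary event when it treats the presenting ACS.
3. Keep death, cardiac arrest and life-threatening arrhythmia counted from randomisation in both arms. Starting the clock at index diagnosis or discharge would make it depend on arm, since the Participant timeline gives minimum stays of 1 hour and 4 hours.
4. Report index ACS and index revascularisation by arm as separate diagnostic-yield outcomes.
5. State which definition the 5.5–7.5% range refers to, and restate the expected rate and power for the definition adopted. If index ACS is kept, give power over a range of plausible rates in place of the single 80%.

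**Cost.** No extra patients are needed to correct the definition, and event times are already adjudicated. It is still a change to a primary component in an open-label trial with 3,560 of 4,800 patients enrolled and DMC interim safety analyses planned. It should be dated, justified, and made by people who have not seen MACE by arm. Removing index events may also lower the rate, which makes the fixed margin larger in relative terms: 2 points is 2/6.5 = 31% of a 6.5% rate but would be 100% of a 2% rate (an assumed figure). The restated power section should say so.

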##### Secondary outcome measures

ᅟ

##### Combined MACE proportion

As described above within 90 and 365 days after randomizationWill be evaluated when inclusion of all patients is completed

##### All-cause mortality

Number of all-cause deaths divided by number of patientsAll-cause mortality registered in the national health registry, occurring from time of admission to discharge, within 30, 90 or 365 days after randomizationWill be evaluated when inclusion of all patients is completed

##### Cardiovascular mortality

Number of cardiovascular deaths divided by number of patients, occurring from time of admission to discharge, within 30, 90 or 365 days after randomizationCause of death is registered in the national register of causes of deathWill be evaluated when inclusion of all patients is completed

##### Survived cardiac arrest

Number of patients surviving an event of cardiac arrest divided by number of patients“Survived cardiac arrest” is determined from registration of out-of-hospital cardiac arrest in Danish register of cardiac arrest and in-hospital cardiac arrest in DANARREST and in the national health registry, occurring from time of admission to discharge, within 30, 90 or 365 days after randomizationThe endpoint committee adjudicates survived cardiac arrest, blinded to the initial randomization.Will be evaluated when inclusion of all patients is completed

##### Confirmed diagnosis of ACS during index admission or re-admission with ACS

Number of ACS events (only first event per patient) divided by number of patientsThe national health registry is used to determine whether the patient is confirmed of having or being re-admitted with ACS, from time of admission to discharge and within 30, 90 and 365 days after randomization. The endpoint committee adjudicates ACS, blinded to the initial randomization. The 2015 ESC Guidelines for the management of ACS in patients presenting without persistent ST-segment elevation and the Universal Definition of Myocardial Infarction will be used to evaluate if the patient had ACS and subsequently classify it as follows:○ Unstable angina pectoris (UAP)○ Non-ST-elevation myocardial infarction (NSTEMI)STEMI○ Bundle branch block myocardial infarctionWill be evaluated when inclusion of all patients is completed

